#### Aim 3: Characterizing Potential Interaction Relationships Established Between Fungal and Bacterial Communities

We will use a metabolomics approach in which sputum samples will be homogenized with methanol for metabolite extraction and derivatization. The extract and derivatives will then be analyzed for chemical composition using quantitative gas chromatography-mass spectrometry technique based on metabolite profiling [40]. Gas chromatography-mass spectrometry–based metabolite raw data will be processed using the XCMS toolbox; this processing will involve peak detection, alignment, and multivariate statistical analysis using the XCMS outputs.

We will also attempt to design a genome-scale metabolic model for pulmonary microbial communities to infer the entire microbiome (bacteria and fungi) and host-microbial interactions under different patient conditions. This will be based on the interplays of genes (identified by metagenomics and inferred from amplicon data) and metabolites (identified by metabolomics) by analyzing the full data set and using specific computational tools, including but not limited to Meta-genomic Operationalized Assembly and Annotation Tool 2 for functional categorization and Human Microbiome Project Unified Metabolic Analysis Network 2 for profiling abundance of microbes and activity of their metabolic pathways. A genome-scale model will be developed to explore complex relationships between microbial components, such as genes, using assembly of gut organisms through reconstruction and analysis, a reconstruction-based tool used for microbial-host metabolism, and interactions’ analysis [41,42]. In this manner, a genome-scale metabolic model will help us to postulate and test the underlined hypotheses that could link the burden, genotype, and phenotype of pulmonary microbial communities. Through these analyses, we also hope to infer ecological relationships, including but not limited to mutualism, commensalism, competition, antagonism, and symbiosis.

### Expected Deliverables

The following will be expected deliverables to be achieved during the project:

Total fungal burden in 406 patients and its changes over time (using quantitative PCR)Fungal microbiome analysis: relative abundance of sputum fungi and their identity (using ITS2 sequencing)Bacterial microbiome analysis: relative abundance of sputum bacteria and their identity (using 16S rRNA gene sequencing)Whole community metagenomics: detailed genomic identification and characterization of abundant members of the sputum microbiome, including gene-level detail Metabolomics profiling of sputum: analysis of host and microbial metabolites in longitudinal sputum samples Integration of culture-dependent and culture-independent data with clinical information to understand disease processes in the patient cohortA genome-scale metabolic model of the diseaseIdentification of fungal and bacteria in the disease to support subsequent epidemiological, treatment, and basic research investigationsTraining and knowledge transfer in cutting-edge microbiome techniques

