**Methods:**

This will be a laboratory-based cross-sectional study, with a sample size of 406 participants. From each participant, 2 sputa samples (one on-spot and one early morning) will be collected. These samples will then be analyzed for both fungal and bacterial etiology using conventional metabolic and molecular (intergenic transcribed spacer and 16S ribosomal DNA–based polymerase chain reaction) approaches. We will also attempt to design a genome-scale metabolic model for pulmonary microbial communities to analyze the composition of the entire microbiome (ie, fungi and bacteria) and investigate host-microbial interactions under different patient conditions. This analysis will be based on the interplays of genes (identified by metagenomics) and inferred from amplicon data and metabolites (identified by metabolomics) by analyzing the full data set and using specific computational tools. We will also collect baseline data, including demographic and clinical history, using a patient-reported questionnaire. Altogether, this approach will contribute to a diagnostic-based observational study. The primary outcome will be the overall fungal and bacterial diagnostic profile of the study participants. Other diagnostic factors associated with the etiological profile, such as incidence and prevalence, will also be analyzed using univariate and multivariate schemes. Odds ratios with 95% CIs will be presented with a statistical significance set at *P*<.05.

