## Methods

### Study Design

This study will be a laboratory-based observational cross-sectional study.

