### Statistical Analysis Plans and Power Calculations (Sample Size)

Based on the preliminary study, the prevalence of fungal coinfections among patients suspected of TB has been previously determined to be 40% using Kish-Leslie formula (n=Z^2^ P (1-P)/ d^2^) for determining the sample size in a cross-sectional study. In this formula, n is the sample size, Z (1.96) is the statistic for the level of confidence, P (0.4) is the estimated prevalence, and d (0.05) is the margin of error for the confidence interval. Using the Open Epi calculator, considering a population of 195,013 for Greater Mbarara, the sample size was determined to be 369 patients. Since we anticipate a 10% dropout rate, we will recruit 406 patients. From these patients, only 2 sputum samples will be collected—an on-spot sample on the day of recruitment and an early morning sample the following day, making a total of 812 samples to be collected. Obtained data will be analyzed using appropriate software, such as GraphPad (GraphPad Software Inc), Stata (StataCorp), or Epi Info (Centers of Disease Control and Prevention), among many others.

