### Conclusions

We present the protocol of a laboratory-based cross-sectional study involving patients with TB-like symptoms. Through this study, we will explore the metabolic and molecular ecological evolution of invasive opportunistic pulmonary fungal coinfections. This will be achieved by determining the fungal burden, characterizing the associated microbial communities and exploring the potential interaction relationships established between fungal and bacterial etiologies. Through this study, we aim to create diagnostic profile schemes that can be used to infer patient prognostic outcomes in at-risk individuals. Establishing key fungal-bacterial cross-kingdom synergistic relationships is crucial for instituting fungal-bacterial coinfecting etiology.

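### Two sputa taken one day apart in a cross-sectional study cannot usefully estimate incidence, and their difference should not be presented as change over time or as longitudinal data

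*Protocol article*

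**What the plan says.** Under Study Design the protocol article states: "This study will be a laboratory-based observational cross-sectional study". The Abstract (Methods) and the Conclusions also call the study cross-sectional.

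The sample size section fixes the sampling. It says "only 2 sputum samples will be collected" per patient, namely "an on-spot sample on the day of recruitment and an early morning sample the following day", "making a total of 812 samples to be collected". The Results section also speaks of two visits. The sample size itself is built for one prevalence.

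Three statements elsewhere go beyond that design:

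- Abstract, Methods: diagnostic factors "such as incidence and prevalence, will also be analyzed using univariate and multivariate schemes".
- Expected Deliverables: "Total fungal burden in 406 patients and its changes over time (using quantitative PCR".
- Expected Deliverables: "analysis of host and microbial metabolites in longitudinal sputum samples".

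A fourth statement is softer. The Conclusions aim at "diagnostic profile schemes that can be used to infer patient prognostic outcomes in at-risk individuals".

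**The concern.** Incidence needs people who are free of the condition at the start and are observed long enough for new cases to arise. Change over time needs samples that differ in time without also differing systematically in something else. Neither condition is met by two samples a day apart when the first is always on-spot and the second always early-morning.

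Three misreadings could follow. Prevalent positivity could be labelled incidence. A difference between specimen types could be labelled a change in fungal burden or in metabolites. Associations seen at enrolment could be read as prognostic. The deliverables name the assay, the number of patients and the kind of sample, so readers will expect those outputs.

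**Working it through.** **1. The plan's own sample size (reproduced).** Inputs from the sample size section: Z = 1.96, P = 0.40, d = 0.05, population 195,013, dropout 10%.

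- n = Z² P(1 − P)/d² = 1.96² × 0.4 × 0.6 / 0.05² = 368.8.
- With the finite-population correction: 368.8 / (1 + 367.8/195,013) = 368.1, rounded up to 369.
- Dropout: 369 × 1.1 = 405.9, rounded up to 406. Samples: 406 × 2 = 812.
- Half-width of the 95% interval, 1.96 × √(0.24/n): 0.0500 at n = 369 and 0.0477 at n = 406.

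The figures 369, 406 and 812 all reproduce. They serve the precision of a prevalence and nothing that depends on time.

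**2. Person-time available for incidence.** The interval between the two samples is about one day.

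- All 406 give both samples: 406/365.25 = 1.11 person-years.
- Only 369 do so: 369/365.25 = 1.01 person-years.
- At risk, if the planned 40% are already positive: 1.11 × 0.60 = 0.67 person-years.
- The article's Previous Findings section gives higher figures for fungal coexistence (70.7%) and colonization (up to 92%). With these as the baseline positive share, 1.11 × 0.293 = 0.33 and 1.11 × 0.08 = 0.09 person-years remain.

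**3. Expected new cases.** The documents give no incidence rate, so the rate is an assumption, shown over a wide range. Expected cases = rate × 0.67 person-years at risk.

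| Assumed rate per person-year | Expected new cases in the whole study |
|---|---|
| 0.1 | 0.07 |
| 0.5 | 0.33 |
| 1 | 0.67 |
| 2 | 1.3 |

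With the higher baseline positivity in step 2 the numbers are smaller still. Even a patient who is negative on the spot sample and positive the next morning is not identifiable as a new case, because the first specimen may simply have missed the fungus.

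**4. Change over time.** In every patient, the first sample is on-spot and the second is early-morning. Let the within-patient difference be D = (effect of one elapsed day) + (effect of early-morning versus on-spot specimen) + error. The order is the same in every patient, so only the sum of the first two terms can be estimated. No analysis of these data separates them. D is a valid measure of how the two specimens compare under routine timing, including one-day repeatability. It is not a measure of change over a disease course.

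**5. Prognosis.** The article describes baseline demographic and clinical history and clinical metadata. It describes no follow-up period and no ascertainment of later outcomes, and none of the three aims sets out a prognostic analysis.

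**The case against.** The strongest defence is that the disputed words do little work. The primary outcome is the diagnostic profile, the sample size serves one prevalence, and the methods under Aims 1 to 3 specify no incidence, temporal or prognostic analysis. The promised odds ratios with 95% confidence intervals suit a cross-sectional study. Two serial sputa are also repeated samples in a minimal sense, and a paired difference can be computed. Finally, a journal article condenses a fuller protocol.

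Much of this stands, and it limits the point in four ways.

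- A reader might infer that the two samples say nothing about within-patient differences. That goes too far: the one-day paired contrast is estimable, and the fault lies in its label and interpretation.
- A reader might infer that no patient outcome is collected. The documents do not support this. The limit of two applies to sputum samples, not to clinical data, and silence in a condensed article is not proof. One can say only that no outcome ascertainment is described.
- A reader might treat prognosis as a contradiction equal to the others. It is a closing aspiration, not a listed deliverable.
- A reader might conclude that mislabelled results are certain. No section prescribes them, so they are a risk only.

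Condensation does not rescue incidence or change over time. The article does not merely omit later sampling; its statement that only two sputa are taken, a day apart, excludes it.

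**Conclusion.** The point holds for incidence and for the time-related deliverables, which conflict with the stated design and sampling. Incidence cannot usefully be estimated: about 0.67 person-years at risk, and about 0.07 to 1.3 expected new cases at an assumed 0.1 to 2 per person-year. This rests on a one-day interval, all 406 patients giving both samples and 40% positive at baseline. Fewer completers or higher positivity would only reduce it. The day-to-day difference is computable but fully confounded with specimen type. That follows from the fixed sample order and needs no numerical assumption.

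The prognostic wording is a secondary matter. The primary outcome, the prevalence estimate and its sample size are untouched.

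**What to change.** - **Abstract, Methods:** delete incidence from the analysed quantities and report prevalence, with the odds ratios already planned.
- **Expected Deliverables:** replace the change-over-time wording for fungal burden, and the longitudinal wording for metabolites, with a within-patient paired comparison of on-spot and early-morning sputum, giving the paired difference and the agreement. State that the difference combines specimen type with one-day variation.
- **Conclusions (secondary):** reword the prognostic aim as cross-sectional association with clinical status at enrolment.

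The cost is wording only, with no new patients, samples or assays. The Results section reports that enrolment is complete, so the change belongs in the analysis specification and in the reports. The downside is that the study claims less. Linkage to a TB treatment register is not proposed as a way to keep prognosis, because the documents mention no such register.

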### Study Safety

Study participants will be patients with infectious diseases and will be subjected to minimal risks during sample collection. However, the study will involve the collection, handling, and processing of contagious infectious human biological materials, such as sputum. Additionally, some of the proposed laboratory procedures will involve the use of hazardous reagents, which raise health and safety issues for both study staff and the general environment. However, to mitigate the anticipated risks, we will perform risk assessment procedures to identify the associated risks. Following risk assessment, we will develop standard operating procedures and comply with Control of Substances Hazardous to Health Regulations. These procedures will highlight health and safety measures conforming to the relevant local, national, or international guidelines. To this end, necessary precautions will be taken to ensure that these legislations are followed by both participants and staff involved in the metabolic and molecular ecological evolution of opportunistic pulmonary fungal coinfections (MeMoF) project.

### Study Registration

After a careful audit of the protocol and design, the study was registered in the International Standard Randomized Controlled Trial Number registry (ISRCTN33572982).

### Ethics Approval

The study has been approved by the Uganda National Council of Science and Technology (HS1233ES) and Mbarara University Research Ethics Committee (MUREC1/7-07/09/20) and will be conducted according to Uganda National and European Union legislation.

### Informed Consent

Target patients will be fully informed of the purpose and procedures of this study, their obligations, potential benefits, and risks. To this effect, an informed consent form was prepared and approved by the institutional review board of Mbarara university for use; the form will be signed voluntarily by each of the study participants prior to enrolment.

## Results

Study design, ethical review, approval, and research registration have all been completed. Patient enrollment commenced in March 2022. Most of the enrolled patients have completed their 2 visits. Patient enrollment was completed in June 2023, and the study results will be submitted for publication in late 2023.

We will share the study findings with the department of Microbiology, Faculty of Medicine, Mbarara University of Science and Technology; Ministry of Health Uganda; and other partner nongovernment organizations working with TB and related coinfections. We will discuss the scope, impact, and limitations of pulmonary fungal coinfections and bacterial fungal synergism based on our study findings. We hope to achieve technical and policy-level interventions, conduct capacity building, and increase public awareness of microbial ecological evolution. Finally, we will write abstracts and manuscripts for international conferences to an international audience and for peer-reviewed journals, respectively.

## Discussion

### Expected Findings

We anticipate that the findings of our study will enhance understanding and awareness of invasive pulmonary fungal coinfections among patients suspected of having TB. We hope that the diagnosis of invasive pulmonary fungal infections will improve, thereby advancing patient prognosis. In this study, we highlight an important aspect of cross-kingdom synergism during infection. In particular, we will highlight that fungal-bacterial coinfection is common among the susceptible cohorts of patients, particularly patients suspected of having TB. Our study aims to establish and characterize a network of microbial communities associated with chronic pulmonary diseases, in addition to TB. In doing so, we also hope to characterize potential interaction relationships established between fungal and bacterial coinfected communities.

### Previous Findings

PTB is the most common opportunistic pulmonary disease, especially among the cohort infected with HIV/AIDS [3,33]. However, the prevalence of TB has been masked by other possible and somewhat endemic infections that can be as common [43-45]. Accordingly, invasive pulmonary fungal coinfections have been highlighted. Several studies show that endemic pulmonary mycoses are not uncommon; however, clinically, many of them manifest with similar signs to TB [45]. This seems to have promoted the misdiagnosis of many pulmonary fungal infections. In other instances of fungal infections, such as aspergillosis, the treatment of PTB is further complicated with residual activation. Thus, in many parts of the world, pulmonary fungal infections continue to be missed or misdiagnosed.

The spectrum of fungal etiology has evolved over the years, expanding from the commonly isolated Candida species to encompass clinically rare but commonly environmental opportunists, such as *Cladosporium* spp*, Acremonium* spp*, Alternaria* spp*, Aspergillus* spp, and *Fusarium* spp, among others. This evolutionary event seems to be directly proportional to a recent dramatic increase in predisposing conditions, such as solid organ transplantation, prolonged chemotherapy, and hematological malignancies, which have more than doubled over the last 20 years.

Although the etiology of chronic pulmonary infections is often attributed to *Mycobacterium tuberculosis*, several data reveal that numerous unappreciated fungal opportunists and other non-TB bacterial pathogens can also coinfect or serve as the primary cause of the chronic pulmonary disease [43,45]. Our preliminary hospital data show that up to 92% of patients suspected of having PTB develop pulmonary fungal colonization. Previously, Njovu et al [35] determined a 70.7% prevalence for pulmonary fungal coexistence among patients suspected of having TB. However, the causal profile of disease by most of these cocolonizers has not been explored yet. The challenge is that current diagnostic approaches are not designed to routinely assess polymicrobial infections, and therefore, may fail to detect the presence of fungal-bacterial coinfections.

In this protocol, we hypothesized that cocolonization of a host by multiple microbial communities is influenced by the environmental frequency and antimicrobial resistance profiles of both commensal bacterial and fungal opportunists; furthermore, understanding the nature, diversity, and environmental origin of these communities will provide important insight into their pathological potential. Sadly, not much attention has been given to the possibility of cross-kingdom etiology linking TB and pulmonary mycoses. Polymicrobial infection of the pulmonary system is not uncommon. Importantly, how the different etiological entities influence each other is mostly unknown. However, stemming from the wider environment, we know that bacteria and fungi interact on several levels and can have various effects within each consortium [4,7,17-26]. Yet the impact of these effects is barely known.

Taken together, our data so far suggest that fungal-bacterial coexistence may influence their virulence attributes and antimicrobial resistance patterns, with relevance to patient outcomes. Therefore, in this project, we will investigate how these cross-kingdom synergistic interactions in the wider environment shape the evolutionary trajectories of fungi and bacteria, priming them for antimicrobial resistance and virulence in mammals. Importantly, the diversity of pulmonary infective fungi and bacteria and their complex population structures pose challenges to the analysis and interpretation of conventional data.

### Strengths and Limitations

The main strength of our study is that it is the first research project to integrate fungal-bacterial interactions at the interface of metabolic and molecular ecological evolution of fungal-bacterial etiology that is conducted using direct patient samples. Thus, the methodological setup has been designed to enhance awareness of fungal etiology and fungal-bacterial interactions among patients suspected of having TB. Through this study, we hope to improve the diagnosis and management of pulmonary coinfections. The downside of the study is purely technical; we anticipate a limitation in our methodological approach to study key co-interaction effects of the etiological agents at the metabolic level. This limitation might be associated with our lack of capacity to perform metabolomics experiments.

### Conclusions

We present the protocol of a laboratory-based cross-sectional study involving patients with TB-like symptoms. Through this study, we will explore the metabolic and molecular ecological evolution of invasive opportunistic pulmonary fungal coinfections. This will be achieved by determining the fungal burden, characterizing the associated microbial communities and exploring the potential interaction relationships established between fungal and bacterial etiologies. Through this study, we aim to create diagnostic profile schemes that can be used to infer patient prognostic outcomes in at-risk individuals. Establishing key fungal-bacterial cross-kingdom synergistic relationships is crucial for instituting fungal-bacterial coinfecting etiology.

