### Approach and Methodology

#### Aim 1: Determining the Burden and Etiological Profiles of Fungal Coinfections Among Patients Suspected of TB

Patients' sputum samples will be collected and cultured on both fungal and bacterial media for either organism’s isolation. The isolates will be identified and profiled accordingly using conventional phenotypic and genomic-based assays. Total DNA will be extracted from the same sputum samples using a bead-beating phenol-chloroform approach. PCR primers targeting region 2 intergenic transcribed spacer (ITS2) will be used to amplify the fungal DNA present in the sputum samples; the amplified DNA will then be sequenced by Illumina MiSeq technology. This approach has been demonstrated to sensitively identify and determine the relative abundance of all fungi present in similar respiratory samples [35]. In this study, we will use this approach to identify the most abundant fungi present and detect any potential coinfections, which maybe challenging to identify using traditional culture methods. Fungal data will be analyzed using Mothur and the R statistical package Phyloseq (R Core Team) and will be speciated with reference to the UNITE2 database. Fungal quantitative PCR will be applied to determine the total burden of fungi present in each sample. Shotgun metagenomics will also be applied to a subset of samples. This metagenomics approach will reveal genomic detail of the fungi present, which will potentially include antimicrobial resistance genes and virulence genes and provide further typing information that reveals common clones or transmission among patients. Using long-read technology, the Oxford Nano pore GridION has the advantage of being a rapid sequencing technology that has shown promise as a rapid point-of-care test for the identification of microorganisms in clinical samples. As such, the use of this technology in this study may also reduce the time until diagnosis for fungal infections.

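### The plan measures fungal detection in sputum but labels the result coinfection, and in the Discussion invasive coinfection, without a stated criterion linking the two

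*Protocol article*

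**What the plan says.** **What is measured.** The sample size section limits collection to two sputa per patient, one on the spot and one the next morning. Under Aim 1, "sputum samples will be collected and cultured on both fungal and bacterial media", and "PCR primers targeting region 2 intergenic transcribed spacer (ITS2) will be used to amplify the fungal DNA present in the sputum samples". Quantitative PCR gives the fungal load of each sample, and a subset goes to shotgun metagenomics. The metabolomics of Aim 3 also uses sputum.

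**What it is called.** Aim 1 is headed as the burden and etiological profile of fungal coinfections, and sequencing is to "identify the most abundant fungi present and detect any potential coinfections". The sample size section states that "the prevalence of fungal coinfections among patients suspected of TB has been previously determined to be 40" per cent. Expected Findings hopes to "enhance understanding and awareness of invasive pulmonary fungal coinfections among patients suspected of having TB" and says the study will highlight that fungal-bacterial coinfection is common in susceptible patients. The Conclusions say "we will explore the metabolic and molecular ecological evolution of invasive opportunistic pulmonary fungal coinfections".

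**What else the article says.** Previous Findings reports that "up to 92% of patients suspected of having PTB develop pulmonary fungal colonization", cites a 70.7% prevalence of fungal coexistence in the same kind of patient, and grants that the part most of these cocolonizers play in disease is unexplored. Strengths and Limitations says "The downside of the study is purely technical" and names only the metabolomic work.

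**The concern.** Culture, ITS2 reads, PCR load and metagenomic reads show that a fungus or its DNA is in the sputum, how much there is, and what genes it carries. Without a further rule they do not separate infection from colonization or oral carry-over, and they say nothing about invasion. A conclusion worded as coinfection, or invasive coinfection, therefore goes beyond the measurement.

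This touches the main result of Aim 1 and what is built on it: the hoped-for gains in diagnosis and management, and the profiles meant to inform prognosis. It also touches the first hypothesis in the Introduction, that the burden of coinfection exceeds what culture suggests. If a patient counted as coinfected on culture or sequencing, adding sequencing could only raise the count. The hypothesis could then be confirmed by assay sensitivity alone.

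**Working it through.** **1. The plan's own sample size.** Inputs from the sample size section: Z = 1.96, P = 0.40, d = 0.05, population 195,013, dropout 10%.

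- n = Z²P(1−P)/d² = 3.8416 × 0.24 / 0.0025 = 368.8, rounded up to 369. With the finite-population correction it is 368.1, again 369.
- 369 × 1.10 = 405.9, rounded up to 406.

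Both stated figures reproduce. The point concerns what P stands for.

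**2. The labels and frequencies side by side.**

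| Section | Term used | Frequency | Patients out of 369 |
|---|---|---|---|
| Sample size | coinfection, suspected TB | 40% | 369 × 0.40 = 148 |
| Previous Findings | coexistence, suspected TB | 70.7% | 369 × 0.707 = 261 |
| Previous Findings | colonization, suspected PTB | up to 92% | 369 × 0.92 = 339 |

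The gaps from the planning value are 70.7 − 40 = 30.7 points and 92 − 40 = 52 points. The 40% and the 92% are both attributed to preliminary work. The article gives no method for either and no rule connecting the three terms. The Introduction adds lower figures for coinfection or infection (15% to 35% in Africa, mainly in people with HIV and TB; 22.2% in people living with HIV), in other populations.

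**3. Measurement against claim.** The Conclusions say the invasive coinfections will be explored by determining fungal burden, characterizing communities and exploring interactions. Each of these rests on sputum, and none bears on invasion. Previous Findings treats colonization as distinct from disease. The limitations do not carry that distinction over to this study's own results.

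**4. Does naming the quantity as detection require more patients?** The half-width with 369 evaluable patients is 1.96 × √(p(1−p)/369):

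- p = 0.40: 5.0 points
- p = 0.707: 4.6 points
- p = 0.92: 2.8 points
- p = 0.50 (widest case): 1.96 × √(0.25/369) = 5.1 points

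The stated 5-point margin is met at all three of the article's frequencies, and all but met at the widest case.

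**The case against.** The strongest defence is that the article never says every positive sputum will be counted as coinfection. The Abstract's primary outcome is an overall fungal and bacterial diagnostic profile. Aim 1 speaks of potential coinfections, and the Expected Deliverables are neutral, listing fungal burden and the relative abundance of sputum fungi. For this study's own purposes, invasive appears only in the Discussion. The plan also collects clinical history, immune status and host metabolites and means to integrate laboratory with clinical data. A case definition may sit in the full protocol, which a condensed article need not repeat.

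Much of this stands. The deliverables need no rewording, and an absent case definition is not by itself a fault here. But the point rests on what the article does state: sputum as the only specimen, coinfection and invasive coinfection as the subject of its conclusions, an advance statement that coinfection is common, and limits that are only technical. The clinical data are not tied to any rule that classifies infection, and the hedge in Aim 1 is dropped in the Discussion.

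A reader might go further and infer that 71% to 92% of patients will be published as diseased. That is a projection from earlier data: the 92% is an upper figure, the 70.7% is called coexistence, and the observed frequency may differ. A reader might also divide 40 by 70.7 or by 92 and conclude that only 57% or 43% of positives would be truly infected. That requires the 40% to be verified infection, fully detected, in the same population as the other figures. The article supports none of this, and the 40% may itself be detection in sputum. For the same reason the 31- to 52-point gap should not be set against the 5-point margin: one reflects differences of label, method or population, the other sampling error.

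**Conclusion.** The concern holds as a mismatch between what is measured and what is claimed. On the measurements described, the study can estimate how often fungi are detected in sputum, alone or with bacteria. It cannot support a statement about invasive coinfection, and the article gives no basis for equating detection with coinfection.

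The spread from 40% to as much as 92% shows that the terms are not used consistently. It does not measure misclassification, and the documents allow no estimate of the share of positives truly infected. The conclusion assumes only that sputum is the sole specimen and that no infection criterion beyond those in the article will be applied. If the full protocol contains one, the article should state it and apply the term coinfection only to patients who meet it.

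This should be fixed before publication. It invalidates neither the assays nor the sample size.

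**What to change.** - In the sample size section and Aim 1, name the estimated quantity *prevalence of fungal detection in sputum (colonization or infection)* and report it with a 95% CI. Say which of the earlier figures the planning value of 40% corresponds to.
- In Expected Findings and Conclusions, delete *invasive* where it describes this study's own aims or conclusions. Reword the statement that coinfection is common as one about codetection of fungi and bacteria.
- In Strengths and Limitations, add that detection in sputum cannot separate infection from colonization or oral carry-over.
- Optionally, where both sputa of a patient are cultured, tabulate growth of the same species in both samples. Present this as reproducibility, not as evidence of infection: the samples are a day apart, and a stable colonizer could grow in both. Aim 1 does not say that both sputa are cultured, so confirm this first.

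The cost is wording and at most one extra table, with no new specimens, assays or patients. Enrollment is reported as complete, so naming and reporting are what can still change. The drawback is a less striking headline.
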